In the current pandemic, the impact of quarantine and physical distancing on the mental health of the general population has been explored only in a few studies, mostly conducted in China, where the pandemic started (23–25). Qiu et al. (26) found that 35% of the population experienced psychological distress; in particular, those more vulnerable to stress and more likely to develop post-traumatic stress disorder were women and individuals aged between 18 and 30 years or older than 60 years. Moreover, people were more concerned about their own health and that of their family members, while less concerned about leisure activities and relationships with friends (24, 27).

After China, Italy has been the first country to face the contagion of COVID-19 and one of the countries with the highest number of deaths due to this coronavirus (http://www.salute.gov.it/portale/nuovocoronavirus/). On March 8, the lockdown status has been declared by the Italian government. This status included the definition of specific containment and quarantine measures, such as the interdiction of all public meetings and strict movement restrictions (i.e., possibility to go out only for working, serious health reasons, or other urgent needs). These containment measures have been prolonged until May 4.

Moreover, the expected psychosocial and emotional reactions to the pandemic observed in the general population may be significantly different in the Chinese and Italian populations due to their socio-cultural characteristics and historical contexts, which obviously impact on people’s behaviors and attitudes. Furthermore, the organization of public health system is different in Italy compared to China and other Eastern Asian countries, also due to financial constraints. In fact, although in those countries the model of care has shifted in the last 20 years to become more similar to a Western model of care, it has to be acknowledged that 20 years is a relatively short period of time, and differences may still persist.

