Methodologically rigorous studies are needed in order to evaluate the impact of COVID-19 and quarantine measures on the mental health of Italian population. These data will help us to develop appropriate interventions for managing the psychosocial consequences of the pandemic (28–30). The present study has been developed with the aims to: a) evaluate the impact of COVID-19 pandemic and its containment measures on mental health of the Italian population; b) to identify the main areas to be targeted by supportive long-term interventions for the different categories of people exposed to the pandemic.

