## Methods

### Design

The “COVID-IT-mental health trial” is a no-profit, not-funded, national, multicentric, cross-sectional population-based trial involving the following eleven sites: University of Campania “Luigi Vanvitelli” (Naples), Università Politecnica delle Marche (Ancona), Università Milano Bicocca, Università “Statale” (Milan), University of Perugia, University of Pisa, Sapienza University of Rome, “Cattolica” University of Rome, University of Trieste, University of Ferrara; the Center for Behavioral Sciences and Mental Health of the Istituto Superiore di Sanità (Rome). The Department of Psychiatry of the University of Campania “Luigi Vanvitelli” in Naples is the coordinating center, which has originally conceived the study idea and design.

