### Data Collection

#### Recruitment Procedure

An online survey has been set up through EUSurvey, a web platform launched in 2013 by the European Commission. The application, hosted at the Department for digital services (DG DIGIT) of the European Commission, is available to all EU citizens at https://ec.europa.eu/eusurvey. The survey will be online from March 30 to June 30, 2020 (https://ec.europa.eu/eusurvey/runner/COVIDSurvey2020). The survey takes approximately 15–30 min to be completed. Participants can stop the survey at any time and save their answers as “draft” on the web-platform. Furthermore, participants can interact with the principal investigator of the study and with all researchers through email messages at any time during and after study participation.

Participants will be subdivided into four groups: a) Group 1—COVID-19 quarantine group. This group includes the general population which are quarantined but not isolated, i.e., those not directly exposed to contagion nor in contact with COVID-19+ individuals; b) Group 2—COVID-19+ group, which includes isolated people directly/indirectly exposed to the virus; c) Group 3—COVID-19 healthcare staff group, which includes first- and second-line healthcare professionals; d) Group 4—COVID-19 mental health, which includes users of mental health services and all those who had already been diagnosed with a mental disorder.

The survey addresses the Italian population aged over 18 years through a multistep procedure: 1) email invitation to health professionals and their patients; 2) dissemination of the link through social media channels (Facebook, Twitter, Instagram) and the mailing lists of national psychiatric associations; 3) involvement of national associations of stakeholders (e.g., associations of users/carers); 4) official communication channels (e.g., university websites; websites of the hospitals directly involved in the management of the pandemic).

The invitation letter includes information on study purposes and confidentiality. The provision of the informed consent is mandatory in order to start the survey.

The snowball sampling procedure—without the definition of strict inclusion/exclusion criteria (except that of age limit)—will give us the opportunity to recruit a large sample of the Italian population and to evaluate the effect of the studied variables on the outcome measures.

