### Data Analysis

Statistical analyses will be conducted according to a multistep plan. Missing data will be handled using the multiple imputation approach (47). Descriptive statistics will be calculated for the dependent and confounding variables. A bilateral alpha of 0.05 is considered, and error and confidence intervals are calculated at 95%.

The analytic plan will include: 1) data cleaning of the online dataset and replacement of missing values; 2) descriptive statistics of the general characteristics of the recruited sample, in terms of levels of depressive and anxiety symptoms, post-traumatic and stress-related symptoms, insomnia, satisfaction with life, suicidal ideation, hopelessness, post-traumatic growth, resilience, coping strategies, and social support; 3) sub-groups analyses based on the level of exposure to the pandemic (i.e., COVID-19 quarantine group vs. COVID-19+ patients group vs. COVID-19 healthcare staff group vs. COVID-19 mental health group); 4) calculation of a propensity score, in order to adjust our findings for the likelihood of being exposed to the pandemic and to the quarantine (48, 49). This method is adopted since it produces a better adjustment for differences at baseline, rather than simply including potential confounders in the multivariable models. The independent variables used for calculating the propensity score will include gender, age, socio-economic status, and geographical region. The obtained propensity score will be used to weight the observations in the multivariable analyses. In the final regression model, the inverse probability weights, based on the propensity score, will be applied in order to model for the independence between exposure to the pandemic/quarantine and mental health outcomes and estimation of causal effects (48, 49); 5) development of a Structural Equation Model (SEM), in order to evaluate the possible role as mediators and moderators of coping strategies, post-traumatic growth and usage of social networks on the severity of depressive and anxiety symptoms, post-traumatic and stress-related symptoms, suicidal ideation, and hopelessness.

In order to improve the external validity and generalizability of our findings, all analyses will be controlled for the impact of confounding variables, such as age, gender, and geographical region.

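### Controlling for age, gender and region adjusts contrasts within the sample; it does not correct who entered the snowball web survey, so population-level statements keep their selection bias

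*Protocol article*

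**What the plan says.** The target is the national population. Aim (a), in the Background, is to "evaluate the impact of COVID-19 pandemic and its containment measures on mental health of the Italian population", and the Design section calls the study a "national, multicentric, cross-sectional population-based trial".

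The primary hypothesis (Primary Outcome) sets DASS-21 levels among respondents against those of an Italian community sample not exposed to the pandemic, and then predicts an ordering of the exposure groups.

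Recruitment is by snowball through an open web link, "without the definition of strict inclusion/exclusion criteria (except that of age limit"). The channels begin with "email invitation to health professionals and their patients" and go on to social media, psychiatric associations' mailing lists, associations of users and carers, and university and hospital websites (Recruitment Procedure).

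The last paragraph of Data Analysis gives the reason for covariate control: "In order to improve the external validity and generalizability of our findings, all analyses will be controlled for the impact of confounding variables". Age, gender and region are the examples given. The only weights described, in step 4, are inverse probability weights from a propensity score for exposure to the pandemic and quarantine, built on gender, age, socio-economic status and region.

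The Discussion accepts that recruitment may partly bias the findings through interest in the topic, and that a web survey may have kept out people without internet access, older people especially.

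**The concern.** The sentence joins a purpose to a method that does not serve it. Controlling for a confounder makes groups within the sample more comparable, which is internal validity. External validity depends on how respondents differ from the population they stand for, and a regression coefficient for age or gender leaves that as it was. The exposure weights do not help either: they balance exposed against less exposed respondents, not respondents against non-respondents.

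Two planned statements depend on levels rather than on within-sample contrasts: aim (a), and the comparison with the community sample. The Discussion relies on the second to offset the cross-sectional design. Whatever separates respondents from the general population enters both. Several recruitment channels run through healthcare staff and people in contact with psychiatric services, so a link between entry into the survey and the outcome is plausible from the article alone. A reader who takes the sentence at face value would think this had been dealt with.

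**Working it through.** The article gives no figure for selection bias, so there is none to reproduce. The check has four parts.

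**Inputs from the article.** More than 20,000 expected respondents, with 10,000 as the ideal target (Discussion); 95% intervals and two-sided alpha of 0.05 (Data Analysis).

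**Assumed inputs, not in the article.** Share of women among respondents w = 0.65 to 0.80; population share 0.51; women score d = 0.2 to 0.4 SD higher.

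**1. Sampling error of one mean, in SD units.** SE = 1/√N.
- N = 20,000: SE = 0.0071, 95% half-width 1.96 × 0.0071 = 0.0139.
- N = 10,000: SE = 0.0100, half-width 0.0196.

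**2. Illustrative bias from sex imbalance alone.** Bias = (w − 0.51) × d.
- Low: (0.65 − 0.51) × 0.2 = 0.028 SD, or 0.028/0.0071 = 4.0 SE.
- High: (0.80 − 0.51) × 0.4 = 0.116 SD, or 16.4 SE.

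**3. Coverage of the population mean by a nominal 95% interval under bias b.** Coverage = Φ(1.96 − b√N) − Φ(−1.96 − b√N).

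| b (SD) | N = 10,000 | N = 20,000 |
|---|---|---|
| 0.01 | 83% | 71% |
| 0.02 | 48% | 19% |
| 0.05 | 0.1% | about 0% |

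At the low illustrative bias of 0.028 SD and N = 20,000, coverage is about Φ(1.96 − 3.96) = 2%.

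**4. Does covariate control remove the bias?** A least-squares fit with an intercept passes through the sample means, so the adjusted mean at the sample's own covariate means is the raw mean. It moves only if evaluated at external margins, which is standardisation and is not what the article describes.

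A simulation shows this: population of 3 million, N = 20,000, residual SD 1. The outcome is 0.15 × female − 0.1 × age band + 0.05 × region + noise. The log-odds of opting in are −4.3 + 0.9 × female − 0.7 × age band + 0.3 × region + g × outcome. All of these values are assumptions.

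| g | Raw bias | After covariate control | Standardised to population margins |
|---|---|---|---|
| 0 | 0.08 | 0.08 | 0.00 |
| 0.1 | 0.18 | 0.18 | 0.09 |
| 0.2 | 0.28 | 0.28 | 0.19 |
| 0.3 | 0.36 | 0.36 | 0.28 |

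Control alone removes none of the bias in the level. Standardising removes it when opting in depends only on the three covariates, and part of it when opting in also depends on distress.

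**Two side checks.** With a weighting design effect of 1.5 or 3, the SE at N = 20,000 is 0.0071 × √1.5 = 0.0087 or 0.0071 × √3 = 0.0122 SD, so calibrated intervals stay narrow. Referral clustering matters less: design effects 1 + (m − 1) × ICC of 1.04 to 1.95 (assumed m = 5 to 20, ICC = 0.01 to 0.05) lower coverage to between 94.5% and 84%.

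**The case against.** The strongest reply is that the article promises less than it may seem to. It says control will improve generalizability; a reader might infer a claim that the sample becomes representative, but nothing says so, and the covariate list is open. A reader might also infer that step 2 reports unweighted population prevalences. It does not: it describes the recruited sample, mentions neither prevalence nor weighting, and the weighting detail could sit in an analysis plan not shown. Both points stand, and the concern does not rest on them. It rests on the stated reason, which no further detail elsewhere would make correct.

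Second, most of the hypotheses are contrasts between groups, where covariate and propensity adjustment are relevant. That stands, although selection may differ between groups. For the community comparison, adjustment could remove imbalance in age, gender and region if individual records from both samples were modelled together. The article does not say this will be done, and it would still leave group mix and interest-driven response untouched.

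Third, the limitations are disclosed. They are, but the Discussion then discounts self-selection by expecting most people to be interested, and offers no analytic correction for either limitation.

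Fourth, the size is assumed. This is correct. The Background's report that the more vulnerable were "women and individuals aged between 18 and 30 years or older than 60 years" comes from a Chinese survey, and the article itself doubts that such results transfer to Italy. With raised risk at both ends of the age range, even the direction of an age-related bias is unclear.

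Finally, calling a snowball sample population-based is mainly terminology, since the recruitment text is open about the method.

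**Conclusion.** The concern holds for population-level statements: aim (a) and the DASS-21 comparison with the community sample. The stated method cannot deliver the property it is credited with, and no other step described corrects entry into the survey.

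On size, the firm part is that sampling error is about 0.007 SD at 20,000 respondents, so a bias of 0.02 SD would already cut coverage of the population mean to 19%. That figure concerns the survey mean; the community comparison also carries the other sample's error, and that sample's size is not given. The range of 0.03 to 0.12 SD is an illustration on an assumed sex imbalance. It is modest in absolute terms, and the 4 to 16 standard errors largely reflect the large sample.

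The article does not support a stronger conclusion that the results will be biased by a known amount or in a known direction, or that the group contrasts are invalid.

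**What to change.** - For overall level estimates and the community-sample comparison, calibrate (rake or post-stratify) to official population margins for age by sex, region and, where collected, education.
- Report results by the four groups, or weight the group mix where external shares exist. Demographic raking does not correct over-recruitment of healthcare staff and mental health service users.
- Use robust or design-based standard errors, and show unweighted figures beside the weighted ones.
- Keep covariate and propensity adjustment for the group contrasts, and restate its purpose as control of confounding in place of external validity.
- State that the intervals exclude residual self-selection and that the results describe a convenience sample.

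The cost is public margins and one weighting step, with no change to recruitment and no new data. Intervals become somewhat wider, though still narrow beside plausible residual bias. Selection driven by distress itself remains: in the simulation, 0.09 to 0.28 SD was left after standardising.

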### Ethics and Dissemination

This study is being conducted in accordance with globally accepted standards of good practice, in agreement with the Declaration of Helsinki and with local regulations. The study protocol has been approved by the Ethical Review Board of the University of Campania “L. Vanvitelli” (Protocol number: 0007593/i).

## Discussion

Our survey will give us the opportunity to describe the impact of the pandemic on the mental health of different subgroups of the Italian population.

In fact, the analyses will be run according to the four subgroups of respondents: the general population not directly affected by the virus (COVID-19 quarantine group); people who have had a direct or indirect contact with the virus (COVID-19+ patients group); those working in health care units as first or second-line staff (COVID-19 healthcare staff group); people with mental health problems, independently from the contact with the virus (COVID-19 mental health). This choice is due to the evidence that stress and traumas have a different impact on different target groups (7, 50–52).

In the COVID-19-quarantine group, we anticipate that the pandemic and the related containment measures will increase the levels of stress, anxiety and depression, as well as other stress-related symptoms. In particular, physical distancing has obviously changed the patterns of daily routine in order to mitigate the spread of the disease, with serious consequences on mental health and well-being in both the short- and long-term (53). Similar consequences would require immediate efforts for developing preventive strategies as well as direct interventions aiming to mitigate the impact of the outbreak on individual and population mental health. The longer the pandemic will last the most the ordinary life of the general population will be seriously affected. In particular, Zhang et al. (23) have highlighted the need to pay attention to the mental health of people who have not been directly infected by the virus though have been forced to stop all their activities during the outbreak. These people represent the most susceptible group to the detrimental impact of quarantine and physical distancing measures adopted during the lockdown. Moreover, during the current pandemic, it is reasonable to expect that the incidence of severe mental disorders will increase, but also that of other mental health disturbances not reaching the threshold for a full-blown diagnosis (3). However, currently available data are based on studies carried out in China and the different socio-cultural context may limit the generalizability of findings to the Italian and Western contexts. Therefore, we consider essential to collect Italian data in order to develop data-driven guidelines for an adequate management of mental health problems during the emergency and the post-emergency phases. In fact, this survey will represent the starting point for developing, validating, and implementing psychosocial supportive interventions (53, 54), as discussed later in this paper.

We hypothesized that Internet and social media can play a buffering role in the development of psychiatric symptoms (25, 55). It may be that online contacts and interactions will limit the detrimental effects of social isolation (56). Moreover, Internet can represent the ideal setting for providing supportive interventions through tele-mental health applications (57–60). However, the positive effect of Internet and social media has to be confirmed yet, since it is only speculative at this stage.

In the COVID-19+ patient group (i.e., those with a direct or indirect contagion), the impact on mental health has been mostly neglected during the acute emergency phase. Of course, this has been due to the fact that the infection is a potentially life-threatening condition, as confirmed by the need for hospitalization in intensive care units for many patients (61). In particular, the experience of being isolated in the hospital, the perceived danger, uncertainty about own physical conditions and the fear of dying alone can be considered risk factors for the development of post-traumatic, anxiety, and depressive symptoms (62, 63). The only study conducted in China so far has documented that over 90% of COVID+ patients admitted to the hospital reported significant post-traumatic stress symptoms (62, 64, 65). Furthermore, the authors found that providing patients with psychoeducational intervention is well received and perceived as helpful and useful by users.

As regards the effects on mental health of those working in health care units as first-line or second-line staff (COVID-19 healthcare staff group), we expect that many health professionals will experience symptoms of burn-out, including mental exhaustion, irritability, detachment from reality, and insomnia. In a survey involving medical and non-medical health workers, Zhang et al. (23) found a higher prevalence of insomnia, anxiety, depressive symptoms, somatization, and obsessive-compulsive symptoms in mental health staff. Moreover, front-line medical staff working in close contact with infected patients (e.g., staff professionals working in the departments of respiratory, emergency, infectious disease, and intensive care unit) showed higher scores on depressive/anxiety symptoms and had a twofold increase in risk to develop a mental health problem (66–69). However, the effect on suicidal ideation of health professionals has not been investigated yet and will be the focus of one of our work-packages.

Finally, the pandemic will affect the mental health status of people who already suffer from mental health problems, independently from the contact with the virus (COVID-19 mental health group). Although the effects of the coronavirus on mental health have not been systematically studied, it is likely that the COVID-19 will have detrimental effects on patients with pre-existing mental health problems. Many patients with severe mental disorders have been overlooked during the pandemic, although they can have a higher risk of contracting the virus and of death considering the higher prevalence of somatic comorbidities compared to general population and the difficulties in accessing health services (70).

However, if protracted, social isolation may increase the risk of recurrences of episodes of mental disorders, beyond triggering the onset of new mental disorders in most vulnerable people. Moreover, objective social isolation and subjective feelings of loneliness are associated with a higher risk of suicidal ideation and suicide attempts (71). For many persons with mental disorders, being alone is a heavy burden, far beyond that experienced by many other persons (72).

In patients with pre-existing anxiety disorders or obsessive-compulsive disorder, we expect an exacerbation or worsening of their clinical symptoms. Moreover, the fact that there is not (yet) a definitive treatment for the COVID infection represents another potential stressor, further increasing the levels of anticipatory anxiety and reducing personal functioning. In our study, both obsessive-compulsive and anxiety symptom clusters will be evaluated through reliable and validated questionnaires.

We believe that our study has several strengths, which should be highlighted. First, this is the first national multicentric, no-profit study carried out in Italy with a rigorous methodology for evaluating the impact of pandemic and quarantine on mental health. Second, the development of a web-based platform for data collection will give us the opportunity to recruit a high number of participants. Based on previous population surveys carried out in Italy, an ideal target would have been 10,000 participants, but this target has been reached in only 7 days. Therefore, we expect to reach more than 20,000 people within the study period. A third relevant strength of our study is the selection of validated and reliable assessment instruments, which are available and validated in several languages. The next step of the project will be to adapt our survey to the European level, by involving several countries. Fourth, several psychopathological dimensions will be evaluated, not only those usually assessed following natural disasters, such as the post-traumatic and depressive-anxious dimensions. In this study, we will also evaluate the obsessive-compulsive spectrum, the suicidal ideation, the maladaptive use of Internet, among the others, which represent novel targets for psychiatrists (73, 74).

Our study has obviously also some limitations. In particular, the study sample includes the adult population only, due to existing restrictions related to the provision of informed consent of children and adolescents in Italy. However, it is likely that the pandemic will have a detrimental impact on the mental health of adolescents as well (75, 76). Moreover, being exposed to a traumatic event during early life is associated with alterations in the social, emotional, and cognitive development and could determine a variety of impairment in the adulthood. The effects of the pandemic on children and adolescents will be evaluated in an *ad hoc* study, in which we will explore the relationship between parents and their underage children during the pandemic. Another limitation is related to the recruitment process, which might partially bias our findings, since only persons interested in the topic of the survey may have voluntarily participated. However, we expect that most people are interested in participating in the survey given the global magnitude of the current traumatic threat with collective psychological and social reactions.

Another possible limitation of our study is the choice to use a web-based online survey, which may have limited the participation of people not having access to the Internet or not familiar with online tools, particularly the elderly. The cross-sectional design of the study does not allow an evaluation of changes over time as regards the levels of severity of symptoms. However, in order to overcome this possible bias, we will compare our findings with those already available from the Italian population (46) and will adopt a propensity score approach in order to understand the impact of the duration of exposure to the pandemic on the risk of developing psychiatric symptoms. With this methodology, we will be able to evaluate the levels of post-traumatic growth and the type of resilience styles in the study population in order to identify possible critical areas to be targeted in the post-acute phase. However, these psychological constructs are slow to change, and this is why we will promote a second wave of the survey, which will start six months after the end of the “lockdown phase” in Italy. Finally, the survey link can be used multiple times in order to allow sharing and re-posting it. This methodological choice could bias the findings, since the same person can potentially compile the survey several times. However, this methodological choice was due to the adoption of the “snowball” sampling, and it is rather unlikely that someone can compile the same long survey more than once.

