### Outcomes

#### Primary Outcome

The primary outcome of the study is the global score at the DASS-21. This choice is due to the fact that this assessment measure has already been used in a large population study carried out in China, thus giving us the opportunity to compare the Italian situation with the Chinese one (45). Our study hypothesis is that the pandemic and the related containment measures are associated with higher levels of depressive and anxiety symptoms in the surveyed population compared to a community Italian sample not exposed to the pandemic (46). Furthermore, a significant difference between groups will be identified (COVID-19 quarantine group = COVID-19 healthcare professional second-line < COVID-19+ group = COVID-19 healthcare professional first-line group < COVID-19 mental health group).

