#### Secondary Outcomes

In the COVID-19 quarantined group, the severity of obsessive-compulsive symptoms, evaluated through the OCI-R, the perceived loneliness and suicidal ideation will be considered as secondary outcome measures.

In the COVID-19+ patient group, the severity of post-traumatic symptoms at the Severity-of-Acute-Stress-Symptoms-Adult scale will be considered. The hypothesis is that post-traumatic symptoms are more severe in this group compared to the other ones.

In the COVID-19 health staff group, the presence of burn-out symptoms, in particular mental exhaustion, and suicidal ideation will be considered. We anticipate that first-line professionals will report higher levels of mental exhaustion and suicidal ideation compared to second-lines staff members.

In the COVID-19 mental health group, the secondary outcome measures will include the adoption of maladaptive coping strategies (e.g., drinking alcohol) and a poor resilience style. Patients with pre-existing mental disorders are expected to adopt more maladaptive coping strategies and poorer resilience styles compared to the other three groups.

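### For people enrolled because of prior mental illness, comparison with a community sample and the planned propensity score cannot stand in for a baseline, so expected worsening in this group cannot be shown

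*Protocol article*

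**What the plan says.** - **Expectation.** Discussion, on the mental health group: "In patients with pre-existing anxiety disorders or obsessive-compulsive disorder, we expect an exacerbation or worsening of their clinical symptoms". The same paragraph links this to the survey: "both obsessive-compulsive and anxiety symptom clusters will be evaluated through reliable and validated questionnaires".
- **Design.** Methods, Design: a "national, multicentric, cross-sectional population-based trial involving the following eleven sites". Recruitment Procedure: "The survey will be online from March 30 to June 30, 2020". Background: "On March 8, the lockdown status has been declared by the Italian government". Every response therefore comes after lockdown began.
- **Group 4.** Recruitment Procedure defines it by use of mental health services or an existing diagnosis of a mental disorder.
- **Reference.** Primary Outcome: depressive and anxiety symptoms in the surveyed population are hypothesised to be higher, "compared to a community Italian sample not exposed to the pandemic (46").
- **Limitation and remedy.** Discussion, limitations: the article concedes that the design cannot evaluate changes in symptom severity. To overcome this, "we will compare our findings with those already available from the Italian population (46") and a propensity score will be used.
- **Propensity score.** Data Analysis lists its variables as gender, age, socio-economic status and geographical region.

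**The concern.** Worsening is a change from an earlier level. The survey holds no earlier level for any respondent, and the article offers an external sample in its place. For the general population that substitution is open to debate but has some logic, because a pre-pandemic community sample is at least the same kind of population. For Group 4 it is not. These people are classified by prior illness, so they would be expected to score above a community sample with or without a pandemic.

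What is at stake is the conclusion that the study may draw. The remedy is stated without exception for Group 4, and the community comparison covers the whole surveyed population. An excess in people with prior illness could thus be presented as an effect of the pandemic.

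**Working it through.** The article states no figure for this comparison, so there is nothing to reproduce. The question is what the planned data can identify.

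**1. What is observed.** Let *g* be the mean difference between Group 4 patients and the community reference before the pandemic, and *w* the mean worsening in Group 4 since then. The comparison estimates

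observed gap = *g* + *w*.

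Neither term is given in the article, and no planned measurement separates them:

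| Source | Does it supply *g* or a Group 4 baseline? |
|---|---|
| Survey, 30 March to 30 June 2020 | No: it opened after 8 March |
| Reference 46 | No, as described: a community sample |
| Propensity score | No: no prior diagnosis or prior severity among its four variables |
| Second wave, six months after lockdown ends | No: it gives a later value, not an earlier one |

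**2. How easily *g* alone gives a significant result.** Set *w* = 0 and SD = 1, with two-sided alpha 0.05 (the alpha in Data Analysis). The standard error is √(1/n₄ + 1/n_c), and the probability of a significant excess is approximately Φ(*g*/SE − 1.96). The article gives no *g*, Group 4 size or reference size, so all three are assumed over a range.

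Worked case: *g* = 0.2, n₄ = 100, n_c = 400. SE = √(0.0100 + 0.0025) = 0.1118; *g*/SE = 1.789; Φ(−0.171) = 0.43.

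| *g* (SD) | n₄ | n_c = 400 | n_c = 1000 |
|---|---|---|---|
| 0.2 | 100 | 0.43 | 0.48 |
| 0.2 | 300 | 0.74 | 0.86 |
| 0.2 | 1000 | 0.92 | 0.99 |
| 0.5 | 100 | 0.99 | >0.99 |
| 0.5 | 300 or 1000 | >0.99 | >0.99 |
| 1.0 | 100 to 1000 | >0.99 | >0.99 |

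The size of the survey does not help. More respondents make *g* + *w* more precise and leave the split unknown.

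**3. Carry-over into the whole-sample comparison.** If a share *s* of respondents belongs to Group 4 and a share *s*₀ of the reference sample has comparable illness, and *g* is now the gap between people with and without prior illness, then prior illness alone shifts the overall mean by (*s* − *s*₀) × *g*. With *s* − *s*₀ assumed between 0.02 and 0.10 and *g* between 0.5 and 1.0 SD, the shift runs from 0.02 × 0.5 = 0.01 SD to 0.10 × 1.0 = 0.10 SD. Recruitment through clinicians' patients, psychiatric associations' mailing lists and user associations makes a positive *s* − *s*₀ plausible, but the article does not give it. This part is small. The problem is chiefly one for claims about Group 4 itself.

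**The case against.** The strongest reply is that the article never plans to test worsening. The sentence is an expectation in the Discussion. The formal Group 4 hypotheses are differences between groups: highest on the DASS-21 (Primary Outcome), and more maladaptive coping and poorer resilience than the other three groups (Secondary Outcomes). A cross-sectional survey can describe both. Data Analysis lists no Group 4 versus community test, so the probabilities above concern a comparison that is not planned in that form. The limitation is also disclosed.

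Much of this stands. A reader might infer that the study will formally declare worsening in Group 4; the article labels no analysis step that way. What remains is that the disclosure is followed by a claim to overcome the limitation, made for all respondents, and the same Discussion predicts worsening in these patients and points to the survey's questionnaires.

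A reader might also infer that obsessive-compulsive symptoms go unmeasured in Group 4, because the OCI-R is named as a secondary outcome only for the quarantine group. That does not follow. Assessment Instruments restricts only the burnout inventory to one group, and the wording "In the COVID-19 mental health group, the secondary outcome measures will include the adoption of maladaptive coping strategies" does not present a closed list.

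Finally, the Discussion intends the propensity score to address duration of exposure. A relation between duration and severity within Group 4 would be of interest, but it compares different people. Without prior severity among the covariates, it does not recover change within patients.

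**Conclusion.** The point holds in a limited form. The stated remedy does not work for Group 4, because group membership, the reference sample and the propensity covariates together leave long-standing illness and worsening inseparable. No size of bias can be given, since the article reports neither *g* nor *w*. The illustration shows only that a significant excess is likely with no worsening: probability 0.43 to 0.99 at a prior gap of 0.2 SD, and at least 0.99 from 0.5 SD, for assumed sizes of 100 to 1000 patients and 400 to 1000 reference subjects.

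The conclusion assumes that reference 46 is what the article says it is, a community sample, with no separate results for people with an existing diagnosis. That source was not available to check. The formal between-group hypotheses for Group 4 are not affected.

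**What to change.** 1. In Primary Outcome and in the limitations part of the Discussion, state that comparison with reference 46 will not be used to infer change in Group 4, and report that comparison with Group 4 excluded or shown separately.
2. In the Discussion of the mental health group, replace the expectation of worsening by an expectation of higher current severity than the other groups on the DASS-21 and OCI-R. The data can show this.

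Both use data already being collected. The cost is a few sentences, one additional line of results and a narrower claim for Group 4.

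Adding retrospective items on change since before lockdown is not recommended. The survey is live and reached 10,000 participants in 7 days, so those early respondents would have no answer, and the items would carry recall error.
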